### Data entry and control

The data for the quantitative part of the study (A) are generated by standardised written questionnaires. The answers to the questionnaires are entered into SPSS 22.0 by a student assistant under the guidance of the research assistant. The entered data are assessed for random duplicate entries (5 − 10 %) by checking their validity and plausibility.

### Data monitoring

#### Data monitoring in the clinics is not planned

##### Case number calculation/sample size

To determine an appropriate sample size, it is assumed that the indicators used to characterise the sample should be described with sufficient precision. Sufficient precision should be applied to continuous indicators if the range of the 95 % confidence interval around a sample mean does not exceed a pre-specified value. For categorical variables, it is analogously assumed that the range of the 95 % confidence interval should not exceed a pre-specified value by a sample proportion. In the case of a continuous variable, the limits mentioned are set at +/- 5 points for a scale with a value range of 0 to 100. In the case of proportions, the range of the 95 % confidence interval should not exceed +/- 10 % points in the range of percentages from 10 to 40 %. The required width of the 95 % confidence interval is achieved with a continuous variable from a sample size of N = 100. In the case of a binary variable in the range between 10 and 40 %, the width of the 95 % confidence interval will be less than 20 % points for sample sizes of 100 or more. To compensate for smaller deviations in the required number of cases, a 20 % larger sample is taken compared to this net number of cases, i.e., N = 120 cases. We also expect a dropout rate of 20 % [37, 38]. Thus, the MEDIAN Klinik Heiligendamm will recruit N = 150, and the Reha-Zentrum Schömberg and the Ostseeklinik Schönberg-Holm will separately recruit N = 100 COVID-19 rehabilitants. For the CG, the MEDIAN Klinik Flechtingen and Bad Salzuflen will recruit N = 75 rehabilitation patients, separately, and the Reha-Zentrum Schömberg and Ostseeklinik Schönberg-Holm will recruit N = 40 rehabilitants per clinic.

### Statistical methods

#### Quantitative analysis

In the course of the study, no predefined hypotheses are confirmed. Rather, the rehabilitation groups are precisely characterised. Comparative analyses are used to determine the relevant differences between the subgroups and the comparison group. Accordingly, we mainly provide descriptive evaluations on the burden of disease as well as on health-related changes during and after rehabilitation.

For the interval-scaled variables, variance analyses with measurement repetition are calculated to evaluate the pre-post differences of the outcomes at the various measurement times. Depending on the data constellation, the t-test for dependent or independent samples is used as a parametric significance test. Non-parametric tests are performed for ordinally scaled data. Subgroup analyses will be planned for sex, age and education as well as risk factors and comorbidities. To classify the findings in COVID-19 patients, the stress manifestations and the measured changes are compared with those in the CG.

In addition to the analysis of the health-related changes in relation to a comparison group, the treatment concepts from different rehabilitation facilities are also examined. The type and extent of the therapy, characteristics of the included rehabilitants, perceived benefits of the rehabilitation and subjectively experienced health improvements are recorded. All calculations are performed with SPSS 22.0.

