### A: quantitative measures

To measure the long-term burden of COVID-19 and the effects of rehabilitation, the study includes four measurement points: at the beginning (t_0_), at the end of rehabilitation (t_1_), six (t_2_) and twelve months after rehabilitation (t_3_). A questionnaire with standardised and validated instruments will be completed by all study participants at each measurement point.

In the rehabilitation clinics, the participants of both groups are recruited consecutively at the same time until the planned number of cases is reached.

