To assess the extent of *physical activity*, questions are asked in conjunction with Menski’s Federal Health Surveys [34].

The moderating variables include comorbidity [35], risk factors and sociodemographic variables [36].

The rehabilitants receive the questionnaires at four measurement points. Some of the outcomes that are not likely to change during rehabilitation are only measured at the beginning of rehabilitation and at catamnesis. These are parameters that probably change only insignificantly during rehabilitation (e.g., comorbidities) or outcomes addressing everyday life and the domestic environment. Table 1 presents the set of core instruments used in the study.

**Table 1 Tab1:** Core set of instruments used in the quantitative part of the study

Dimensions	Instruments	t_0_	t_1_	t_2_	t_3_
Restriction of Participation	IMET [17]	●		●	●
Quality of Life	VR12 [20]	●		●	●
Depression, Anxiety and Stress Scale	DASS [22]	●	●	●	●
Stress-Related Psychomental Limitations and Disorders	GAD-7 [23]; PHQ-9 [24]	●	●	●	●
Corona-associated Life Events	Single Items	●	●	●	●
Effects of Chronic Obstructive Pulmonary Disease	CAT [26]	●	●	●	●
Fatigue	EORTC-FA 12 [32]	●	●	●	●
General State of Health	Single Items	●	●	●	●
Performance in Various Areas of Life	QGmR [30]	●		●	●
Occupational Changes	Single Items from QGmR [30]			●	●
Occupational Situation	Single Items	●		●	●
Ability to Work	Work Ability Score, WAS [28]	●		●	●
Subjective Prognosis of Employment	SPE-Scale [29]	●		●	●
Moderating Variables					
Comorbidity	Single Items [35]	●		●	●
Risk Factors	Single Items	●	●	●	●
Sociodemographic Data	Single Items [36]	●		●	●

*t*_0_baseline/right before rehabilitation; *t*_1_ 3-week follow-up/right after rehabilitation; *t*_2_ 6 months after rehabilitation, *t*_3_ 12 months after rehabilitation

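### Repeated-measures ANOVA keeps only participants with every modelled wave; with 20% dropout expected, a mixed model on all returned questionnaires is a cheap improvement

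*Protocol article*

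**What the plan says.** The Quantitative analysis section of the protocol article names the longitudinal method for interval-scaled variables: "variance analyses with measurement repetition are calculated to evaluate the pre-post differences of the outcomes at the various measurement times". It adds that, depending on the data, "the t-test for dependent or independent samples is used as a parametric significance test", and that "All calculations are performed with SPSS 22.0". The same section describes the evaluation as largely descriptive: "we mainly provide descriptive evaluations on the burden of disease as well as on health-related changes during and after rehabilitation".

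The section on quantitative measures says that "the study includes four measurement points": start and end of rehabilitation, then six and twelve months later. The Outcomes section qualifies this: "Some of the outcomes that are not likely to change during rehabilitation are only measured at the beginning of rehabilitation and at catamnesis". Table 1 accordingly gives four waves to DASS, GAD-7/PHQ-9, CAT and fatigue, and three waves (t0, t2, t3) to IMET, VR-12, performance, WAS and SPE.

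The sample-size section states "We also expect a dropout rate of 20" per cent, without saying by which wave. The article does not say how a participant with a missed wave enters the ANOVA. The covariates and propensity matching in the Limitations section deal with differences between the COVID-19 group and the comparison group (CG), not with missing questionnaires.

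**The concern.** In its classical form, repeated-measures ANOVA needs a value at every wave in the model. A participant who misses one wave is removed, together with the waves that he or she did return. The article therefore pairs a method that needs complete follow-up with an explicit expectation of incomplete follow-up over twelve months.

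Two things are at stake. The first is precision: usable questionnaires are thrown away. The second is selection. The outcomes are fatigue, mood, participation and work ability, and whether someone keeps answering may depend on exactly these. If it does, the completers' means differ from those of the recruited group. If the dependence differs between COVID-19 and CG participants, part of that difference passes into the group comparison. An exploratory aim does not protect a description from selection.

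**Working it through.** **1. The plan's own figures.** With half-width = 1.96 × SD / √n, n = 100 and an assumed SD of 25 give 4.90, inside the ±5 limit. The article states no SD; the limit implies at most 5 × √100 / 1.96 = 25.5. For a proportion of 40%, the width is 2 × 1.96 × √(0.24/100) = 19.2 percentage points, below 20. Then 100 × 1.2 = 120 and 120 / (1 − 0.20) = 150, the recruitment target of the largest clinic. The totals also agree: 150 + 100 + 100 = 350 and 75 + 75 + 40 + 40 = 230. The stated figures reproduce.

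**2. Complete cases at 20% dropout.** 350 × 0.80 = 280 and 230 × 0.80 = 184. The 150-patient clinic keeps 120, which is the number planned for.

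**3. Missed single waves.** Let q be the share of non-dropouts missing each follow-up wave (an assumption) and k the number of follow-up waves (3 or 2, from Table 1). The complete fraction is 0.80 × (1 − q)^k.

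| q | k = 3: COVID-19 / CG | k = 2: COVID-19 / CG |
|---|---|---|
| 0% | 280 / 184 | 280 / 184 |
| 5% | 240 / 158 | 253 / 166 |
| 10% | 204 / 134 | 227 / 149 |
| 15% | 172 / 113 | 202 / 133 |

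At q = 10% and k = 3 the 150-patient clinic keeps 150 × 0.583 = 87.5, with half-width 1.96 × 25 / √87.5 = 5.24, just above the limit. If the 20% were instead lost independently at each follow-up wave, 0.8³ = 0.512 would leave 179 and 118 for four-wave outcomes.

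**4. What ANOVA costs against a paired test.** If the 20% is spread evenly over three intervals, 0.8^(1/3) = 0.928 remain at t1, so about 325 of 350 have a t0–t1 pair. The ANOVA uses 280. With equal SD, its standard error for that change is √(325/280) = 1.08 times as large, or 8% more, even when dropout is unrelated to health.

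**5. Bias.** Simulation of 400,000 participants, all inputs assumed: 0–100 scale with high scores meaning greater burden, true means 50, 42, 40 and 40, SD 25, equal correlations, 20% total dropout, dropout log-odds rising by b per SD of the last observed score.

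| Correlation | b | Completers' wave means minus truth, t0 to t3 | Bias in t0–t3 change |
|---|---|---|---|
| 0.5 | 0 | −0.02, −0.05, −0.02, −0.03 | −0.01 |
| 0.5 | 0.5 | −1.75, −1.77, −1.73, −1.31 | 0.44 |
| 0.5 | 1.0 | −3.17, −3.19, −3.19, −2.39 | 0.79 |
| 0.7 | 0 | −0.08, −0.07, −0.03, −0.03 | 0.05 |
| 0.7 | 0.5 | −2.15, −2.13, −2.10, −1.81 | 0.34 |
| 0.7 | 1.0 | −3.88, −3.85, −3.83, −3.34 | 0.54 |

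Likelihood-type estimates from all available data stay within 0.1 point throughout.

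**6. Scale.** With 280 completers, a wave mean has standard error 25/√280 = 1.49 and half-width 2.93, so a bias of 1.3 to 3.9 is 0.9 to 2.6 standard errors. The t0–t3 change has SD 25 × √(2(1 − r)), i.e. 25.0 for r = 0.5 and 19.4 for r = 0.7, and standard error 1.49 or 1.16. Its bias of 0.3 to 0.8 is about 0.3 to 0.5 standard errors.

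**7. Group comparison.** If both groups drop out by the same mechanism, the biases largely cancel. If only one group's dropout depends on health, that group's bias carries over in full: under 1 point for the difference in t0–t3 change, up to about 4 points for a difference in completers' wave means.

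**The case against.** Several stronger conclusions are tempting, and the document does not support them.

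- A reader might infer that the paired t-tests share the defect. They do not: such a test needs only the two waves compared, and it loses only incomplete pairs.
- A reader might take every outcome to need four questionnaires. Table 1 gives five of the instruments three waves, so a missed t1 excludes nobody from those.
- A reader might conclude that the reported burden will be wrong at every wave, baseline included. That would require the descriptive summaries to be restricted to ANOVA completers. The article calls its evaluation mainly descriptive and sets no such restriction; t0 can be described in everyone who answered at t0.
- A reader might say that the 20% dropout undermines the planned precision. At the 150-patient clinic it is already in the recruitment figure; only missed single waves would be an extra loss.

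Two further objections have weight. The ANOVA is stated for changes between waves, where the calculated bias is small. And the simulation lets dropout depend on the last observed score, which is the situation that a likelihood analysis handles. If people stop answering because of their current, unrecorded state, a mixed model is biased too.

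Finally, this is a condensed article, and missing-data handling may be set out in the full protocol, so its absence here is not the complaint. What stands is narrower. The article does name a method, that method in its usual form discards incomplete participants, and nothing shown replaces or supplements it.

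**Conclusion.** The point holds as a criticism of the named ANOVA alone. At the plan's own 20% dropout it uses about 280 of 350 COVID-19 and 184 of 230 CG participants, fewer if single waves are missed, and drops the questionnaires that the others returned.

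Bias is possible, not certain. It is about zero if dropout is unrelated to the outcome. With SD 25, correlations of 0.5 to 0.7 and a log-odds slope of 0.5 to 1.0 per SD, it is about 1 to 4 points in completers' wave means and under 1 point in the t0–t3 change. The SD, correlations, slopes and missed-wave shares are all assumptions; the article gives none of them. Since the study is exploratory and nothing stated becomes invalid, this is a cheap improvement and not a must-fix.

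**What to change.** In the Quantitative analysis section, replace repeated-measures ANOVA by a linear mixed model for repeated measures, fitted by REML with SPSS MIXED:

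- time as a categorical factor, with group and group × time;
- unstructured covariance over the waves scheduled for that outcome in Table 1 (four or three);
- all returned questionnaires, whether or not the participant answered every wave;
- changes from t0 to each later scheduled wave, and their COVID-19 versus CG differences, reported as model contrasts with 95% confidence intervals.

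Keep the complete-case ANOVA as a sensitivity analysis, and state the number of participants behind each result.

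The cost is one paragraph of wording and slightly more analysis work, with the same data and software. The limit should be stated alongside it: the model corrects only for dropout that depends on observed data.

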### Qualitative analysis of the interviews and expert workshop

The interviews and focus group are analysed using qualitative content analysis [39–41]. We use MAXQDA 12 for coding. The transcripts are checked for relevant topics and interesting content to finally develop a category system. The main topics are derived from the research questions and the interview guide; subcategories are induced from materials developed, e.g., in subsumption [40]. To test the category system, independent test coding is performed by two researchers; then, the categories and definitions are modified. The entire coding process is developed in the form of a consensual coding [42], i.e., the transcriptions are coded independently by two scientists. Finally, the coding is consolidated to develop a consensus.

## Discussion

The novelty of the disease and the increasing use of rehabilitation services by COVID-19 patients enhances the call for research. At present, COVID-19 rehabilitation does not follow uniform guidelines. Therefore, it is necessary to review the different therapeutic approaches and to formulate recommendations for pneumological rehabilitation after COVID-19. Furthermore, the rehabilitation needs of COVID-19 patients and their rehabilitation capacity will be assessed. The concrete short-, medium- and long-term effects of COVID-19 medical rehabilitation have not yet been evaluated.

When assessing rehabilitation, it is also essential to analyse rehabilitation aftercare. To date, there is no evidence on the needs at the end of rehabilitation, nor is there a uniform approach to rehabilitation aftercare. This study clarifies which aftercare recommendations are given to these rehabilitants, to what extent they are realised and how the needs of the rehabilitants are met.

It now appears that COVID-19 survivors of any disease severity seek rehabilitation. Therefore, the study results are also differentiated against the different degrees of severity and additionally contrasted with a comparison group. Finally, recommendations for rehabilitation and rehabilitation aftercare need to be developed for COVID-19 patients.

### Innovation factor

 During the telephone interviews and written survey, the study participants are asked about their aftercare recommendations, the use of aftercare programmes and their wishes or needs for the time after rehabilitation. By classifying the results on the basis of a comparison group, conclusions are drawn for further projects on suitable aftercare strategies in the novel indication COVID-19. Further study could aim at maintaining long-term rehabilitation effects and maintaining or restoring employability. In addition, it may be possible that different recommendations are made for the varying severity of the disease course; therefore, further consideration is necessary.

### Immediate expected results of the project

As this is an observational study, the baseline situation and the changes in the mentioned outcomes are described. These results are reported in relation to the comparison group, and statements on the extent to which there are similarities and differences are provided. The rehabilitation contents, needs and ability; aftercare recommendations and their implementation are also described descriptively for different degrees of disease severity.

Although the rehabilitants do not receive an intervention in the strict sense, they all undergo rehabilitation. Based on previous studies on pneumological rehabilitation as well as from the current experience of rehabilitation physicians, we expect positive changes in outcomes during rehabilitation. For example, we expect a significant reduction in the burden of disease and psychological impairments at the end of rehabilitation. The extent to which the effects on outcomes change over all four measurement points will be described in this study.

The results of the study will show whether rehabilitants have different needs in terms of rehabilitation, its contents and aftercare due to their individual course of illness, their previous illnesses or other personal prerequisites. With regard to aftercare, it is assumed that individual needs range from their own initiative and classic aftercare programmes to more intensive aftercare.

### Transferability of the project results to the everyday care situation

In recent months, it has become apparent that the need for rehabilitation services for COVID-19 survivors is increasing. To offer a treatment that meets the needs of rehabilitants, appropriate research is necessary. At the end of the present study, practical recommendations for rehabilitation after COVID-19 will be developed. A common consensus in the rehabilitation procedure after COVID-19 can guarantee a universal standard in German rehabilitation.

The observational study is conducted in five German rehabilitation clinics. However, it is possible to transfer the results and provide recommendations to other pneumological rehabilitation clinics.

### Limitations

To ensure equal treatment, all characteristics of the participants (e.g., age, education) and the disease (e.g., severity of the disease, disease status, and comorbidity) are documented and compared between groups. If differences arise between the two groups, they are comparably integrated in the analysis (e.g., as covariates in multivariate methods or by propensity score matching). Based on our present knowledge, we assume that structural changes in the context of this project are very unlikely.

## Data Availability

The datasets generated and/or analysed during the current study are not publicly available due to the data protection regulations and declarations of consent of the study participants. The declarations of consent exclude the release of the data for external analyses. A sample declaration of consent is available from the corresponding author on request. The study results are published and thus made available to all those interested in the study. The study protocol, the dataset at the participant level and the statistical code for generating the results are not publicly available.

## Abbreviations

CG: Comparison group
COPD: Chronic obstructive pulmonary disease
COVID-19: Coronavirus disease
DRV Bund: Deutsche Rentenversicherung Bund
DSM-IV: Diagnostic and Statistical Manual of Mental Disorders
ICF: International Classification of Functioning, Disability and Health
ID: Identification number
IPD: Individual participant data
PHQ-D: Patient Health Questionnaire
PSM: Propensity score matching
